##### Consent process

Written, informed consent will be obtained from all participants prior to enrolment. A sample informed consent from may be viewed in Additional file 2.

##### Subject discontinuation and withdrawal

Subjects may voluntarily withdraw from study participation at any time. If a subject is removed from the study, an attempt should be made to obtain laboratory and clinical evaluations that would have been obtained at the completion of the study. If the subject is removed because of an adverse event, they should remain under medical care and observation by their treating physician as long as appropriate.

##### Follow-up evaluation

Patient will be seen 6 weeks post treatment to evaluate short-term treatment toxicity. If patients cannot travel for this visit (or refuse to travel), an attempt will be made to contact the patient by phone to complete follow-up information. It must be documented if follow-up information is being gathered by telephone. The FACT-G and EQ-5D-5L quality of life questionnaire will be completed at that visit. Further follow-up will be according to physician discretion; a recommended frequency would be every 3 months at minimum. Follow-up investigations will be at the physician’s discretion. While routine reimaging is not required, a follow-up CT of the head, chest, abdomen, and pelvis at 3 months post-treatment or at the time of symptomatic progression is suggested.

#### Statistics and sample size calculation

##### Sample size

A minimum of 3 patients will be accrued. Assuming a worst case scenario where the maximum number of patients accrued cannot be planned and require additional enrolment, a maximum of 48 patients will be accrued to this Phase I dose escalation study (12 per dose level).

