### Study design

This is a modified 3 + 3 design Phase I dose escalation trial. Participants will be from a single tertiary academic radiotherapy department in Canada. Three patients will initially be treated at dose level 1, 12 Gy in 2 fractions over 2 weeks, with evaluation of toxicity occurring 6 weeks after completion of treatment. If the composite co-primary endpoints are met, subsequent dose escalations will be accomplished by increasing the number of 6 Gy weekly fractions up to a maximum dose level of 30 Gy in 5 fractions over 5 weeks (Fig. 1). Given the potentially wide variety of anatomic scenarios for polymetastatic disease and the potential planning challenges beyond clinical tolerability, dosimetric planning feasibility will be evaluated with a planning success rate of greater than 33% deemed as acceptable for each dose level. Thus, a total of 12 patients per dose level could potentially be accrued to fully determine the clinical and technical feasibility.

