##### Dose escalation criteria

For a given dose level, toxicity as DLT will be assessed after three patients have been treated at a given dose level at the 6-week assessment post treatment. If all three patients meet the co-primary safety endpoint, escalation to the next dose level will occur. If two or three patients fail the co-primary safety endpoint, the MTD will be determined as the dose level preceding the failed dose level. If one patient fails the co-primary safety endpoint, an additional three patients will be accrued at that dose level. If one or more of these additional three patients fail the co-primary safety endpoint, the MTD will be determined as the dose level preceding the failed dose level. If all three additional patients meet the co-primary safety endpoint (i.e. a cumulative five of six patients pass the co-primary safety endpoint), dose escalation to the next level will occur. All patients at a given dose level must be assessed for 6-week toxicity before escalation to the next dose level can occur.

Treatment planning futility will be considered if less than 33% of the patients (to a maximum of 9 patients) at a specific dose level can successfully have a treatment plan generated for that dose level meeting organ at risk constraints. If treatment planning futility is encountered, the MTD will be considered as the dose level preceding the failed dose level.

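### The worst-case maximum of 12 per level and 48 in total does not carry the 33% planning threshold through to the six evaluable patients that an expanded level needs

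*Protocol article*

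**What the plan says.** All references are to the protocol article.

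- **Accrual cap.** Sample size sets the maximum: "a maximum of 48 patients will be accrued to this Phase I dose escalation study (12 per dose level"). Its stated basis is: "Assuming a worst case scenario where the maximum number of patients accrued cannot be planned and require additional enrolment". Study design repeats the cap: "Thus, a total of 12 patients per dose level could potentially be accrued to fully determine the clinical and technical feasibility".
- **Planning threshold.** Study design has "a planning success rate of greater than 33% deemed as acceptable for each dose level". Dose escalation criteria calls planning futility at "less than 33% of the patients (to a maximum of 9 patients").
- **Who is evaluable.** Treatment plan and Treatment planning both keep a patient who cannot be planned at the target level out of the 3+3. That patient is treated lower, followed, and counted as a planning failure at the higher level.
- **Safety rule.** Under Dose escalation criteria, "toxicity as DLT will be assessed after three patients have been treated at a given dose level". Then: "If one patient fails the co-primary safety endpoint, an additional three patients will be accrued at that dose level". Escalation after that first failure requires all three additional patients to pass, that is, five of six. One or more further failures puts the MTD at the preceding level.

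**The concern.** Planning failures use up enrolment but supply no evaluable patients. The cap must therefore allow for planning failure wherever evaluable patients are needed, including the expansion cohort. A figure of 12 seems to make that allowance only once.

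The trial's objective is to establish the MTD. If a level that has passed planning feasibility reaches its cap before the safety rule is satisfied either way, the MTD must be settled ad hoc or the stated maximum exceeded.

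**Working it through.** **Inputs from the article:** 3 evaluable patients in the first cohort; 3 more if exactly one fails, so 6; planning threshold 33%, judged on at most 9 patients; cap 12 per level; 4 escalation levels.

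**Inputs assumed:** the article gives neither a true planning rate p nor a true safety failure rate q. I take p from 1/3 to 80% and q at 10%, 20% and 30%, with patients independent.

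**1. Reproducing the stated figure.** The article does not show its derivation, but this fits:
- first cohort: 3 / (1/3) = 9 enrolled
- expansion: 3 enrolled, all planned
- 9 + 3 = 12 per level; 12 × 4 = 48

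The same 12 also equals 6 / 0.50. Either way, six evaluable patients in 12 means a planning rate of at least 6/12 = 50%.

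**2. Carrying the threshold through.**
- 3 of 9 is 33.3%, not below 33%, so the level continues. At that rate, 6 / (1/3) = 18 per level and 18 × 4 = 72.
- If the Study design wording is read as requiring at least 4 of 9, 6 / (4/9) = 13.5, so 14 per level and 14 × 4 = 56.

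Both exceed 12 and 48.

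**3. A path with no decision.** Three of the first 9 are planned and one of those three fails safety. One of the next 3 is planned and passes. The level now has 12 enrolled, 4 evaluable and 3 passing.
- Escalation needs five of six: not met.
- Setting the MTD at the preceding level needs two failures: not met.
- Futility needs under 33% planned: 4/12 = 33.3%, not met. Extending futility to 12 patients does not help, since 4/12 and 5/12 (41.7%) are both above 33%.

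**4. How often.** A level ends undecided only if all of these hold: at least 3 of the first 9 are planned; exactly one of the first three evaluable patients fails; the total T planned among 12 is 3, 4 or 5; and none of the T − 3 additional evaluable patients fails. So

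P(undecided) = 3q(1 − q)² × Σ P(T = t and at least 3 of first 9 planned) × (1 − q)^(t − 3), for t = 3, 4, 5.

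Example, p = 1/3 and q = 20%:
- P(T = 3, 4, 5 and not futile) = 0.0809, 0.1821, 0.1821
- weighted sum = 0.0809 + 0.1821 × 0.8 + 0.1821 × 0.64 = 0.343
- P(exactly one of three fails) = 3 × 0.2 × 0.8² = 0.384
- product = 0.343 × 0.384 = 0.132

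| True planning rate | Not futile at 9 | Not futile and fewer than 6 planned of 12 | Undecided, q = 10% | q = 20% | q = 30% |
|---|---|---|---|---|---|
| 1/3 | 62.3% | 44.5% | 9.5% | 13.2% | 13.1% |
| 40% | 76.8% | 43.3% | 9.1% | 12.4% | 12.1% |
| 50% | 91.0% | 29.7% | 6.1% | 8.2% | 7.7% |
| 60% | 97.5% | 13.3% | 2.7% | 3.5% | 3.3% |
| 70% | 99.6% | 3.4% | 0.7% | 0.9% | 0.8% |
| 80% | over 99.9% | 0.4% | 0.1% | 0.1% | 0.1% |

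**5. Is 18 a ceiling?** No. At p = 1/3, P(at least 6 planned of 18) = 58.8%, so 41.2% of such levels would still fall short of six.

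**The case against.** The other side has several fair arguments.

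- **The sum is not wrong.** 9 + 3 and 12 × 4 are correct. The dispute is about an unstated assumption for the expansion cohort. This stands: it is not an arithmetic slip, and 12 is enough whenever at least half the patients can be planned.
- **Low planning rates are not forecast.** The 33% is a floor, and eligibility requires the treating oncologist to believe that all sites can be safely planned. This favours higher rates but does not prove them, and the plan itself accepts rates down to its threshold.
- **The harm is easily overstated.** P(at least 6 planned of 12) is 17.8% at one third, 33.5% at 40% and 61.3% at 50%. A reader might take the complements as the chance of a stalled level. They are not: a stall also needs a level that is not futile, exactly one early failure, and no later failure, because a later failure is itself a decision.
- **No added exposure to higher doses.** A reader might infer that the gap lets escalation proceed unsafely. It does not: a stalled level fails the condition for escalating. What stays open is the MTD and the accrual ceiling.
- **The article is a condensation.** A rule for reaching the cap may sit in the full protocol, so its absence here is not the finding. The conflict between the printed worst-case label, the threshold and the six-patient requirement remains.

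**Conclusion.** The concern holds in a limited form. As printed, 12 and 48 are not the worst case for planning failure under the plan's own 33% threshold. They cover an expanded level only if at least 50% of its patients can be planned. The printed cap, threshold and escalation rule together leave an end state without a decision.

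The size depends on assumed rates. For safety failure rates of 10% to 30%, the chance per level opened is about 10% to 13% at a planning rate of one third, 6% to 8% at 50%, 3% to 4% at 60%, and under 1% at 70% or more. The problem arises only when a level is expanded.

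A reader might conclude that 72 is the correct maximum. The documents do not support that: 18 per level is the enrolment at which six plannable patients are expected at exactly one third, and it gives no guarantee.

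This should be fixed, but it does not invalidate the design.

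**What to change.** 1. Restate the basis of the maximum in Sample size and Study design, and in the Abstract where 48 recurs. Either:
   - keep 12 and 48, say that they assume at least 50% plannability when a level is expanded, and stop calling them the worst case; or
   - give about 18 per level and 72 in total at the 33% threshold, described as a planning figure.
2. Reconcile Study design, Sample size and Dose escalation criteria so that the cap, the planning threshold and the escalation rule together yield a decision when the cap is reached with fewer than six evaluable patients. If the full protocol already has such a rule, cite it. The content of the rule is for the investigators. It should be consistent with the 33% threshold, which 4 or 5 planned of 12 does not fall below.

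The first option costs wording only. The second raises the stated maximum by 72 − 48 = 24 patients. Neither changes the 3+3 rule.

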##### Dose escalation criteria

For a given dose level, toxicity as DLT will be assessed after three patients have been treated at a given dose level at the 6-week assessment post treatment. If all three patients meet the co-primary safety endpoint, escalation to the next dose level will occur. If two or three patients fail the co-primary safety endpoint, the MTD will be determined as the dose level preceding the failed dose level. If one patient fails the co-primary safety endpoint, an additional three patients will be accrued at that dose level. If one or more of these additional three patients fail the co-primary safety endpoint, the MTD will be determined as the dose level preceding the failed dose level. If all three additional patients meet the co-primary safety endpoint (i.e. a cumulative five of six patients pass the co-primary safety endpoint), dose escalation to the next level will occur. All patients at a given dose level must be assessed for 6-week toxicity before escalation to the next dose level can occur.

Treatment planning futility will be considered if less than 33% of the patients (to a maximum of 9 patients) at a specific dose level can successfully have a treatment plan generated for that dose level meeting organ at risk constraints. If treatment planning futility is encountered, the MTD will be considered as the dose level preceding the failed dose level.

##### Analysis plan

Descriptive statistics will be used to characterize the patient demographics on the study, distribution of lesions treated and dosimetric parameters of the treatments and toxicity experienced at 6 weeks. Progression free survival will be tracked and reported using Kaplan Meier statistics. Changes in QOL will be reported as the minimal clinically important change comparing pre and post treatment scores by patient.

##### Data and safety monitoring committee

The DSMC will meet annually after study initiation to review toxicity. The DSMC will review the chart of any case of grade 4–5 toxicity to determine if such toxicity is related to treatment. If the DSMC deems that toxicity rates are excessive (> 40% grade 4 toxicity, or any grade 5 toxicity), then the DSMC can, at its discretion, recommend cessation of the trial, dose adjustment, or exclusion of certain treatment sites and/or delivery techniques that are deemed as high-risk for complications.

##### Confidentiality of subject records

All study participant personal health information will be kept strictly confidential. All participants will be identified using initials and a unique identification number. The master list (confidential subject identification list) linking participants to their unique identification number will be kept strictly confidential by the principal investigator. Public reports of the study will not contain any names of participants.

##### Protocol amendments

The trial protocol will be amended only through approval by the principal investigator (current version: 1.0, protocol date July 28, 2020). It will be the responsibility of the principal investigator to disseminate amendments to co-investigators, the research ethics board and trial registries. Authorship of the trial abstract and manuscript will be decided by the principal investigator at the time of submission.

## Discussion

This novel phase I trial seeks to investigate the MTD of SABR delivered to patients with polymetastatic cancer who have exhausted (or refused further standard of care) systemic therapy options. We believe that initial evaluation with a rigorous phase I trial is necessary to determine what treatment dose can be safely considered in patients with polymetastatic cancer prior to embarking on evaluation of the potential efficacy of this treatment modality.

Precedent for the treatment of extensive metastatic disease with radiotherapy exists in the experience of using hemi-body radiotherapy for palliation of diffuse bone metastases [22], as well as the use of radio-ligand or systemic radiopharmaceuticals for the treatment of metastases [23]. Treating the entire body with total body radiation is not feasible due severe bone marrow and gastrointestinal tract dysfunction, side effects seen when total body irradiation is purposefully given as part of a stem cell transplant [24]. However, with modern radiation planning software and delivery platforms, we believe it is feasible and practical to give SABR to all sites of polymetastatic disease while minimizing doses to organs at risk.

Further rationale for exploring SABR in the polymetastatic setting comes from emerging randomized evidence that supports aggressive radiotherapy to the primary tumour, either with SABR or conventional (chemo) radiation in patients newly diagnosed with polymetastatic prostate [25] and nasopharyngeal cancers [26]. For these tumour types, improvements in progression-free and overall survival have been observed with reasonable side effect profiles. Sites of oligometastatic/polymetastatic disease were not routinely treated with radiotherapy in these studies, leading to the hypothesis that outcomes could possibly be improved further with the addition of SABR, assuming it can be safely delivered.

In designing this trial, we chose to evaluate dose levels in incremental fractions of 6 Gy for several reasons. First, this dose level represents familiarity in the context of hemi-body radiotherapy. While hemi-body radiotherapy has fallen out of favour due to enhancements in systemic therapy and improvements in radiopharmaceuticals, the experience of using this technique serves as the rationale behind using 6 Gy fractions of SABR. The starting dose of 12 Gy in 2 weekly fractions should also be expected to offer palliation of symptomatic metastases. Second, by escalating the number of fractions but keeping the dose per fraction consistent, an optimal radiotherapy treatment plan can be generated for the target dose level. If this optimal treatment plan does not to meet dose constraints at the target dose level, the number of fractions can be easily decreased without needing to generate a new radiotherapy plan. This allows for increased efficiency of workflow in a setting where we anticipate treatment plan generation will be resource intensive and time consuming. Third, delivering the fractions once per week allows for careful evaluation of potential, unanticipated toxicity during treatment. For example, we are carefully evaluating for the possibility of bone marrow suppression due to SABR, particularly in our chosen patient population who have exhausted (or refuse) further lines of systemic therapy and may have pre-existing myelosuppression. Finally, while the doses of SABR within this trial would not typically be considered below truly ablative doses, we believe the maximum dose level will strike an acceptable balance between anticipated efficacy, treatment intent, and potential toxicity.

Our study population was carefully considered for creation of this novel phase I trial. We chose to evaluate a subset of patients where systemic therapy use at the time of SABR is unlikely to interfere acutely with the evaluation of the MTD, as no standard systemic therapy options are available (or are refused by the patient). It is also unlikely that any toxicity from SABR in this study would interfere with the possibility of receiving subsequent systemic therapy that may become available or the patient chooses to access. However, patients enrolled on this study are expected to have been heavily pretreated with systemic therapy, which may influence secondary endpoints in our trial such as progression-free survival and overall survival. Some have argued phase I trials should be offered earlier in the treatment pathway for patients [27], though we believe the toxicity of SABR in this setting needs to be carefully evaluated before earlier implementation can be considered. Whether there is an upper limit to the number of lesions that can safely be targeted in SABR remains to be seen. For this trial, we have arbitrarily chosen 50 targets. More likely, it is the relative distribution, size, and proximity of metastases to critical organs at risk that will determine the maximum number of lesions that can safely be treated. Valuable information regarding the variety of anatomic scenarios when considering polymetastatic disease will be gained through this experience.

## Conclusion

ARREST is a novel phase I trial leveraging the availability of modern image guided radiotherapy for the treatment of polymetastatic disease. Such treatment, if shown to be safe and tolerable, may provide additional treatment options for patients with extensive metastases who are ineligible or unwilling to undertake palliative systemic therapies.

## Data Availability

Not applicable.

## Abbreviations

18-FDG: 18-flurodeoxyglucose
4D-CT: Four-dimensional computed tomography
ALT: Alanine aminotransferase
AST: Aspartate aminotransferase
CT: Computed tomography
CTCAE: Common toxicity criteria for adverse events
CTV: Clinical target volume
eGFR: Estimated glomerular filtration rate
EQ-5D-5L: EuroQol 5 Dimension, 5 Level
FACT-G: Functional assessment of cancer therapy: general
GGT: Gamma glutamyl transpeptidase
GTV: Gross tumour volume
IMRT: Intensity modulated radiotherapy
INR: International normalized ratio
ITV: Internal target volume
MRI: Magnetic resonance imaging
MTD: Maximally tolerated dose
PSMA: Prostate specific membrane antigen
PTV: Planning target volume
SABR: Stereotactic ablative radiotherapy
VMAT: Volumetric modulated arc therapy
